### 8.7 Premature termination of the study

The study may be discontinued for one of the following reasons:

- a serious adverse event which is possibly, probably or definitely related to the infection with female *Schistosoma mansoni* cercariae;
- >50% of subjects in a dose group (more than 1 out of 3 from group A or more than 5 out of 10 from groups A and B) experience a grade 3 adverse event, possibly, probably or definitely related to infection with female *Schistosoma mansoni* cercariae and persisting at grade 3 for >48 hours during the 20 weeks follow-up;
- on advice from the SMC;
- on advice from the investigator, pending discussion with the SMC;
- on advice from the accredited METC.

## 9. SAFETY REPORTING

### 9.1 Temporary halt for reasons of subject safety

In accordance to section 10, subsection 4, of the WMO, the sponsor will suspend the study if there is sufficient ground that continuation of the study will jeopardise subject health or safety. The sponsor/investigator will notify the accredited METC without undue delay of a temporary halt including the reason for such an action. The study will be suspended pending a further positive decision by the accredited METC. The investigator will take care that all subjects are kept informed.

### 9.2 AEs, SAEs and SUSARs

#### 9.2.1 Adverse events (AEs)

Adverse events are defined as any undesirable experience occurring to a subject during the study, whether or not considered related to infection with female *Schistosoma mansoni* infection. All adverse events reported spontaneously by the subject or observed by the investigator or his staff will be recorded.

#### 9.2.2 Serious adverse events (SAEs)

A serious adverse event is any untoward medical occurrence or effect that

- results in death;
- is life threatening (at the time of the event);
- requires hospitalisation or prolongation of existing inpatients' hospitalisation;
- results in persistent or significant disability or incapacity;
- is a congenital anomaly or birth defect; or
- any other important medical event that did not result in any of the outcomes listed above due to medical or surgical intervention but could have been based upon appropriate judgement by the investigator.

An elective hospital admission will not be considered as a serious adverse event.

A grade 3 AE will not be considered a SAE per se.

The investigator will report all SAEs to the sponsor without undue delay after obtaining knowledge of the events. The sponsor/investigator will report the SAEs through the web portal *ToetsingOnline* to the accredited METC that approved the protocol, within 7 days of first knowledge for SAEs that result in death or are life threatening followed by a period of maximum of 8 days to complete the initial

preliminary report. All other SAEs will be reported within a period of maximum 15 days after the sponsor has first knowledge of the serious adverse events.

### 9.2.3 Suspected unexpected serious adverse reactions (SUSARs)

Adverse reactions are all untoward and unintended responses to an investigational product related to any dose administered.

Unexpected adverse reactions are SUSARs if the following three conditions are met:

1. the event must be serious (see chapter 9.2.2);
2. there must be a certain degree of probability that the event is a harmful and an undesirable reaction to the medicinal product under investigation, regardless of the administered dose;
3. the adverse reaction must be unexpected, that is to say, the nature and severity of the adverse reaction are not in agreement with the product information as recorded in:
  - Summary of Product Characteristics (SPC) for an authorised medicinal product;
  - Investigator's Brochure for an unauthorised medicinal product.

The sponsor will report expedited the following SUSARs through the web portal *ToetsingOnline* to the METC:

- SUSARs that have arisen in the clinical trial that was assessed by the METC;
- SUSARs that have arisen in other clinical trials of the same sponsor and with the same medicinal product, and that could have consequences for the safety of the subjects involved in the clinical trial that was assessed by the METC.

The remaining SUSARs are recorded in an overview list (line-listing) that will be submitted once every half year to the METC. This line-listing provides an overview of all SUSARs from the study medicine, accompanied by a brief report highlighting the main points of concern.

The expedited reporting of SUSARs through the web portal Eudravigilance or *ToetsingOnline* is sufficient as notification to the competent authority.

The sponsor/investigator will report expedited all SUSARs to the competent authorities in other Member States, according to the requirements of the Member States.

The expedited reporting will occur not later than 15 days after the sponsor has first knowledge of the adverse reactions. For fatal or life threatening cases the term will be maximal 7 days for a preliminary report with another 8 days for completion of the report.

#### **9.2.4 Adverse events data collection**

Safety assessments will be performed, and recorded by the investigators. All adverse events/reactions (solicited and unsolicited), observed by the investigators or by the subject, will be accurately documented in the case report form by the investigators.

For each event/reaction the following details will be recorded:

1. Description of the event(s)/reaction(s)
2. Date and time of occurrence
3. Duration
4. Intensity
5. Relationship with the intervention
6. Action taken, including treatment
7. Outcome

Symptoms will be ranked as (1) mild, (2) moderate, or (3) severe, depending on their intensity according to the following scale:

- Mild (grade 1): awareness of symptoms that are easily tolerated and do not interfere with usual daily activity
- Moderate (grade 2): discomfort that interferes with or limits usual daily activity
- Severe (grade 3): disabling, with subsequent inability to perform usual daily activity, resulting in absence or required bed rest

For fever, the following scale will be used:

- Mild (grade 1): 37.5 - 38.0°C
- Moderate (grade 2): > 38.0 to 39.0°C
- Severe (grade 3): > 39.0°C

Temperature will be measure tympanically.

If an AE changes in frequency or intensity during the specified reporting period, these changes will be documented in the eCFR. The highest severity grade will be noted in the eCFR.

When an AE/SAE occurs, it is the responsibility of the investigators to review all documentation (e.g. hospital progress notes, laboratory, and diagnostics reports) related to the event. The investigators will then record all relevant information regarding an AE/SAE on the eCRF or SAE Report Form, respectively.

The investigator will attempt to establish a diagnosis of the event based on signs, symptoms, and/or other clinical information. In such cases, the diagnosis should be documented as the AE/SAE and not the individual signs/symptoms.

#### **9.2.5 Assessment of causality**

The investigators are obligated to assess the relationship between study procedures and the occurrence of each AE/SAE. The investigators will use clinical judgment to determine the relationship. Alternative causes, such as natural history of the underlying diseases, concomitant therapy, other risk factors and the temporal relationship of the event to the challenge will be considered and investigated. The relationship of the adverse event with the study procedures will be categorized as:

- Not related: A relationship to the administration of the *Sm* female cercariae cannot be reasonably established; another etiology is known to have caused the adverse event or is highly likely to have caused it.
- Unlikely: A relationship to the administration of *Sm* female cercariae is unlikely; however, it cannot be ruled out.
- Possible: There is a potential association between the event and administration of the *Sm* female cercariae; however, there is an alternative etiology that is a more likely.
- Probable: Administration of the *Sm* female cercariae is the most likely cause; however, there are alternative reasonable explanations, even though less likely.
- Definitely: Administration of the *Sm* female cercariae is the cause; another etiology causing the adverse event is not known.

When a regulatory authority requests a binary classification (related vs. unrelated), definitely, probably and possibly related are considered to be “related,” while not related and unlikely related are considered to be “unrelated.” Thus, an intervention-related AE refers to an AE for which there is a possible, probable or definite relationship to the study intervention. The investigator will use clinical judgment to determine the relationship.

### 9.3 Annual safety report

In addition to the expedited reporting of SUSARs, the sponsor will submit, once a year throughout the clinical trial, a safety report to the accredited METC.

This safety report consists of:

- a list of all suspected (unexpected or expected) serious adverse reactions, along with an aggregated summary table of all reported serious adverse reactions, ordered by organ system, per study;
- a report concerning the safety of the subjects, consisting of a complete safety analysis and an evaluation of the balance between the efficacy and the harmfulness of the medicine under investigation.

### 9.4 Follow-up of adverse events

All AEs will be followed until they have abated, or until a stable situation has been reached. Depending on the event, follow up may require additional tests or medical procedures as indicated, and/or referral to the general physician or a medical specialist. SAEs need to be reported until week 20 of the study within the Netherlands.

### 9.5 Safety committee

For this study, a safety monitoring committee (SMC) will be appointed which will be independent of the investigators and sponsor and has no conflict of interest with the sponsor of the study. This SMC will consist of three experienced clinicians qualified to evaluate safety data from clinical studies with schistosome infections. Their main responsibility will be assessing safety reports or serious adverse events and advising the sponsor/investigator on trial continuation. Dose will be escalated 10 weeks after infection, i.e. 2 weeks after treatment, of a dose group, whereby <100% of volunteers were infected (showed detectable serum CAA). This can be a group of 3 or a group of 10 volunteers. The SMC can advise the sponsor of the trial not to escalate the dose, stop the trial, withdraw individual subjects or suspend further study procedures. Should the sponsor decide not to fully implement the advice of the SMC, the sponsor will send the advice to the reviewing METC, including a note to substantiate why (part of) the advice of the SMC will not be followed.

## 10. STATISTICAL ANALYSIS

### 10.1 Primary study parameter(s)

#### 10.1.1 Frequency and severity of adverse events

All volunteers exposed to female *Sm* cercariae will be included in the intention to treat analysis. The safety and tolerability of controlled infection with female *Sm* is evaluated by tabulating all adverse events for each volunteer in an intention to treat analysis. Adverse events will be analysed by calculating the proportion of volunteers in each group who reported mild, moderate or severe adverse events. Given the very small group size, adverse events will mostly be descriptive. If relevant, statistical testing will be performed using chi-square tests or Fisher's exact tests.

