## 7. NON-INVESTIGATIONAL PRODUCT: praziquantel

### 7.1 Name and description of non-investigational product(s)

#### Praziquantel

All volunteers will be treated with 60 mg/kg praziquantel at week 8 and week 12 after infection. Praziquantel is the only drug registered for the treatment of schistosomiasis. Cure rates with a single dose of 40 mg/kg has been reported to vary between 40-90% [4, 5] in endemic areas, however in travelers the efficacy appears lower [14] which may be caused by lower infection intensity or differential host-immune responses. Therefore, repeated praziquantel doses may be required to achieve full cure. A common side effect of praziquantel (>10%) is fatigue. Other less common side effects are abdominal discomfort, nausea, and dizziness. For a summary of findings from non-clinical and clinical studies, please refer to the “bijsluiter” (SPC Praziquantel). Praziquantel has been described to temporarily impair skilled tasks, and thus volunteers treated with praziquantel will be advised not to drive a car or operate machinery on the day of treatment with praziquantel and the day thereafter [15]. They are instructed to take praziquantel after a meal preferably containing high-fat, and high carbohydrate content [16].

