### **Safety laboratory evaluation**

During the study, blood samples will be drawn to assess safety of infection. The blood sampling schedule is depicted in the flowchart (figure 3). Safety analysis include:

complete blood count (including automated differential count of white blood cells), erythrocyte sedimentation rate, creatinine, potassium, bilirubin, AF, gGT, AST, ALT.

Biological safety parameters will be measured on plasma or serum samples at the central laboratory of the LUMC. Assessment of successful infection will be performed by serum CAA measurements at the department of Molecular Cell Biology of the LUMC at 8 weeks after exposure to cercariae. Another assessment of CAA levels will be performed at week 20 to confirm cure. If volunteers are not cured after two doses of praziquantel, a third round of treatment will be given and its effect on CAA levels monitored. *Schistosoma mansoni* antigen detection tests will be performed retrospectively on all samples, unless

the investigator, safety monitoring committee or accredited METC requests specific testing of certain samples for clinical judgment of adverse events.

In the case where a safety laboratory assessment is outside the reference range for the laboratory, a decision regarding whether the result is of clinical significance or not shall be made by the investigator and shall be based, in part, upon the nature and degree of the observed abnormality. The assessment may first be repeated for confirmation. In all cases, the investigator will document in the source documents, the clinical considerations (i.e., result was/was not clinically significant and/or medically relevant) in allowing or disallowing the subject to continue in the study. Since elevated eosinophils are an expected result of this study this measure will not be marked as abnormal in the eCRF. The maximum amount of blood drawn is 560 ml for the 20 weeks study period.

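### Section 9.4 ends SAE reporting at week 20, against section 9.2.2 and just when a third praziquantel round may start; secondarily, the safety table pools praziquantel and infection reactions without a way to label the drug's share

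*Protocol*

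**What the plan says.** **SAE window.** Protocol section 9.4 states: "SAEs need to be reported until week 20 of the study within the Netherlands". Section 9.2.2 obliges the investigator to report every SAE to the sponsor, and the sponsor or investigator to report SAEs to the ethics committee within set deadlines. It gives no last week. Section 9.2.1 defines adverse events over the whole study. Section 8.3 (Follow-up after infection) records them at all follow-up visits, the last being at one year, and section 12.5 ends the study at the last visit.

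**Retreatment.** Section 8.3 (Safety laboratory evaluation) measures CAA at week 20 to confirm cure and adds: "If volunteers are not cured after two doses of praziquantel, a third round of treatment will be given".

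**Safety analysis.** Section 10.1.1 names its target as "The safety and tolerability of controlled infection with female" *S. mansoni*. The method is "tabulating all adverse events for each volunteer in an intention to treat analysis", followed by "calculating the proportion of volunteers in each group who reported mild, moderate or severe adverse events".

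**Causality.** Section 9.2.5 asks investigators to "assess the relationship between study procedures and the occurrence of each AE/SAE", but all five categories are worded for cercariae. *Possible* is used where "however, there is an alternative etiology that is a more likely", and it counts as related in the binary classification.

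**Praziquantel.** Every volunteer is treated at weeks 8 and 12. Section 7.1 says: "A common side effect of praziquantel (>10%) is fatigue".

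**The concern.** The week-20 sentence in 9.4 and the open-ended duty in 9.2.2 cannot both be followed after week 20. The weeks in dispute are the ones in which a volunteer with persisting infection is retreated. Section 13.1 b describes this as the first controlled human exposure to female cercariae. Section 8.7 also lists a related SAE as a reason for discontinuing the study, with no time limit on that criterion, so a late SAE could bear on volunteers in later dose groups.

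The second matter is interpretive. Fatigue, malaise and gastrointestinal complaints appear both among the praziquantel effects (section 11.3) and on the solicited list (section 8.3). A table meant to describe tolerability of the infection will therefore include drug reactions. Section 11.3 also says that praziquantel side effects track the intensity of infection before treatment. Drug reactions could then rise with cercarial dose and look like a dose-response of the infection itself.

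**Working it through.** **1. SAE window, provisions side by side**

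| Provision | Section | End point |
|---|---|---|
| SAE reporting | 9.4 | week 20 |
| SAE reporting | 9.2.2 | none stated |
| AE recording at visits | 8.3 | one-year visit |
| AE definition | 9.2.1 | whole study |
| Diary and round-the-clock physician cover | 8.3 | week 20 |
| Test of cure | 8.3 | week 20 |
| Third praziquantel round, if not cured | 8.3 | at or after week 20 |
| Next scheduled visit after week 20 | Figure 3 | week 52 |

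Time after the cut-off: 52 − 20 = 32 weeks, and 32/52 = 0.615, or 62% of the year. A third round cannot come before the week-20 result that triggers it, so it always falls at or beyond the limit in 9.4.

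**2. Size of the praziquantel share**

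The protocol gives no figure of its own to reproduce here. Inputs:
- two rounds per volunteer (sections 7.1 and 7.2);
- groups of 3, then 7 more to make 10 (section 3);
- praziquantel fatigue above 10% (section 7.1). I take q = 10% per round as the floor. The per-round reading is an assumption.

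The correlation between rounds is not given, so I show both ends.

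Per volunteer, at least one praziquantel event:
- same volunteers react both times: q = 0.10;
- independent rounds: 1 − (1 − q)² = 1 − 0.9² = 0.19.

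At least one such volunteer in a group of n:
- n = 3: 1 − 0.9³ = 0.271, up to 1 − 0.81³ = 0.469;
- n = 10: 1 − 0.9¹⁰ = 0.651, up to 1 − 0.81¹⁰ = 0.878.

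The expected count in a group of 10 is 1.0 to 1.9.

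The protocol gives no upper figure. If q were 30% (assumed), the ranges would be 66–88% for n = 3 and 97–99.9% for n = 10.

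For a single symptom that infection causes in 30% of volunteers (assumed), the pooled proportion with independent rounds is 1 − 0.7 × 0.9² = 0.433 at q = 10%, and 1 − 0.7 × 0.7² = 0.657 at q = 30%.

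**3. What the causality scale can and cannot do**

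The pooling comes from 10.1.1, which uses neither relatedness nor period. The scale in 9.2.5 does not cause it. If applied, the scale would send a recognised drug reaction to *unlikely* or *not related*, because concomitant therapy must be weighed as an alternative cause. What it lacks is a label for praziquantel, so such events merge with all other unrelated ones. Where the cause is uncertain, *possible* applies and the event counts as related to cercariae. Section 13.1 b puts acute schistosomiasis syndrome at three to ten weeks. The uncertainty is therefore greatest in weeks 8–10, where timing alone does not separate the two causes.

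**The case against.** **On SAEs.** A reader might infer that 32 weeks pass with no SAE reporting at all. The protocol does not support that. Section 9.2.2 has no end date, SUSAR reporting (9.2.3) has no week-20 limit, the annual safety report (9.3) runs throughout the trial, and 9.4 itself follows events until they resolve or stabilise. One could also read 9.4 as the specific rule that limits 9.2.2. That would remove the contradiction but leave the gap after a third round. The third round concerns only volunteers who are not cured.

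**On pooling.** Tabulating all events is sound practice, and a breakdown by period or relatedness may sit in an analysis plan that is not shown. A reader might infer that the trial cannot separate drug from infection reactions. That goes too far: section 9.2.4 records date, duration, relationship and action taken for each event, so a before/after split is possible from planned data. What an analysis plan could not recover is an attribution to praziquantel that was never collected.

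**On size.** Section 13.1 i expects adverse effects in nearly all volunteers, and 16 of 17 had a rash in the male-cercariae study. An any-mild-event proportion would therefore hardly move. This stands: the 10–19% matters for symptom-level and higher-grade summaries.

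**On the stopping rule.** A reader might infer that praziquantel reactions would trigger section 8.7. Its grade 3 criterion is already limited to cercariae-related events that persist at grade 3 beyond 48 hours in more than half a group, so no change is needed there.

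**Conclusion.** The week-20 limit in 9.4 is the firm part. It conflicts with 9.2.2 and sits badly with 9.2.1 and 8.3. It also falls exactly where a conditional third praziquantel round begins, with 32 weeks (62% of the year) and one scheduled visit remaining. This rests on the text alone, and a separate analysis plan would not change the reporting duty.

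The pooling in 10.1.1 is a real but secondary weakness. At the 10% floor, 10–19% of volunteers would carry a praziquantel event, with at least one in 27–47% of groups of 3 and 65–88% of groups of 10. The lower ends assume fully correlated rounds, the upper ends independent ones, and the 10% is read as per round.

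It might seem to follow that the period before praziquantel should be the primary one. It does not, because infection events in weeks 8–10 would then drop out of the main table.

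**What to change.** 1. Reconcile section 9.4 with 9.2.2 so that SAEs are captured and reported through the week-52 visit, including after any third praziquantel round. The week-52 visit already exists, so the cost is slightly more reporting work.
2. In section 9.2.5, add a separate causality item for praziquantel, and for artemether/lumefantrine where it is given. This costs one more eCRF field.
3. In section 10.1.1, keep the all-event table and supplement it with a breakdown by onset before or after the first praziquantel round and by attributed cause. Onset dates are already collected, so this costs one extra table.

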## 8. METHODS

### 8.1 Study parameters/endpoints

#### 8.1.1 Main study parameter/endpoint

- Frequency and severity of adverse events after controlled human *Schistosoma mansoni* infection with female cercariae
- The number of female cercariae at which 100% volunteers show detectable *Schistosoma mansoni* circulating anodic antigen

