### 11.3 Benefits and risks assessment, group relatedness

There is no benefit of participation in the trial for the individual volunteer. Therefore the risk and discomfort of participation for individual volunteers should be carefully weighed against the scientific advantage of the controlled human *Schistosoma mansoni* infection model, in particular for vaccine and drug development. The CoHSI model has the potential to be extremely instrumental to vaccine and drug discovery and clinical testing for the widespread disease of *Schistosoma mansoni*, with an enormous global disease burden, and as such may have unprecedented repercussion for public health. Moreover,

the development of a female-only controlled human *Sm* infection model in addition to the previously established male-only model will allow further exploration of sex-specific immune responses.

The risks associated with participation in this study are related to infection with female helminths from the species *Schistosoma mansoni*. Several aspects should be considered in the risk assessment:

1. Risks of infection with female *Schistosoma mansoni*

Please refer to section 2.3.2 of the Product Dossier for a description of the clinical experience with *Schistosoma mansoni* infections in travelers and the male controlled human *Schistosoma mansoni* infection.

In summary, three main complications could occur following infection with female *Schistosoma mansoni* cercariae:

a. Swimmer's itch

A discrete urticarial rash at the site of entry of cercariae. The chances of this complication occurring is very likely, however, we expect the rash to be very mild as the number of cercariae penetrating the skin is low. In the CoHSI1 study 16 out of 17 volunteers reported a mild rash at the site of infection. All these rashes started within two days after the exposure and severity peaked one week after infection. None of the rashes required treatment. In case severe discomfort occurs, the urticarial rash can be treated with local triamcinolone cream 0.5%.

b. Acute schistosomiasis syndrome

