#### i. Predictability of effect

We expect that adverse effects of the infection will be observed in nearly all of the volunteers. Most volunteers will experience cercarial dermatitis at the site of infection (16 out of 17 in our previous trial with male cercariae). This is expected to resolve without intervention and none of the volunteers in the previous trial needed symptomatic treatment. Higher doses appeared to prolong the duration of the rash. Next, symptoms related to acute schistosomiasis infection are likely to occur in volunteers. In our previous study, there appeared to be some suggestion of higher risks with higher infection doses, however due to small sample size, statistical evidence for a dose-response relationship was difficult to assess. Because female worms are hypothesised to dampen innate host immune responses, the incidence of symptoms of acute schistosomiasis syndrome may be smaller in this study. The risk of morbidity related to oviposition is low, because the number of eggs secreted will be much lower than in a natural, mixed infection. In addition,

egg-related morbidity is positively associated with infection intensity and duration of infection. Our infection will be of low intensity (potentially similar to those observed in travelers) and of limited duration (8 weeks). The risk of side effects of praziquantel treatment increases with infection intensity, and therefore this risk is relatively low in our study.

The presence of *Schistosoma* worms can be detected with the UCP-CAA test. This test is the most sensitive and quantitative assay available to detect schistosome antigen. In baboons, we were able to show proof of concept by detecting low numbers of *Schistosoma* worms (figure 12, Product Dossier). However, the occurrence of adverse events (particularly acute schistosomiasis syndrome) may not be related to the level of antigen detected. Therefore, antigen levels are in principle only determined retrospectively and close clinical monitoring is required to ensure optimal safety and timely treatment of symptomatic volunteers.

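### The only by-dose adverse event summary in section 10.1.1 is near its ceiling for common mild reactions and cannot show the effect of dose on rash duration that the protocol reports

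*Protocol*

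**What the plan says.** Section 8.1.1 makes safety one of the two main endpoints: "Frequency and severity of adverse events after controlled human" infection with female cercariae. Section 10.1.1 gives the analysis in two parts. The first is a listing, "tabulating all adverse events for each volunteer in an intention to treat analysis". The second is the only summary at dose-group level, "calculating the proportion of volunteers in each group who reported mild, moderate or severe adverse events". The section adds "Given the very small group size, adverse events will mostly be descriptive" and, where testing is thought relevant, "statistical testing will be performed using chi-square tests or Fisher's exact tests". Both tests are for proportions.

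Section 10.1.1 does not say whether grades are pooled or shown separately. It also does not say whether a volunteer with events of several grades counts once or several times, or whether the proportions are by symptom or by relatedness. Duration is not mentioned.

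Other sections bear on the choice. Section 13.1(i) states "We expect that adverse effects of the infection will be observed in nearly all of the volunteers" and reports of the previous trial "Higher doses appeared to prolong the duration of the rash". Section 11.3 gives the rate: "In the CoHSI1 study 16 out of 17 volunteers reported a mild rash at the site of infection". Section 9.2.4 has duration recorded for every event, along with the highest grade and changes in intensity. Section 8.3 has volunteers keep a diary of adverse events to week 20.

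**The concern.** A summary that counts whether a volunteer ever had an event can separate doses only if some volunteers do not have it. For the mild, near-universal reactions the protocol itself expects almost everyone to have it, at any dose. The dose effect that the protocol reports for the commonest of these, rash, lay in how long it lasted. The measure named for comparing doses is therefore insensitive to that effect, although the data that would show it are collected.

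At stake is the usefulness of one part of a main endpoint in a dose-escalation trial. If rash or another common symptom lasts longer at higher doses, the by-dose table in section 10.1.1 would look the same in every dose group.

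**Working it through.** The protocol states no sample size, power or alpha for safety, so there is no planned figure to reproduce. The check has four parts.

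**Inputs.** Rash in the previous trial: 16/17 = 94.1%, mild, pooled over its dose groups (section 11.3). Its exact 95% confidence interval is 71.3% to 99.9%. Group sizes: 3, or 3 + 7 = 10 at one dose (section 3). Acute schistosomiasis syndrome in the previous trial: 2 of 3 at 30 cercariae, and 2 of 11 with severe events suggestive of it at 20 cercariae (section 11.3). Two-sided alpha of 0.05 is assumed where a test is considered.

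**1. Ceiling for the common mild reaction.** With true rate p, the chance that every volunteer in a group of n is counted is pⁿ.

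- n = 3: (16/17)³ = 4096/4913 = 0.834.
- n = 10: (16/17)¹⁰ = 0.545.
- A group of 3 and a group of 10 both complete: (16/17)¹³ = 0.455.

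These figures carry the male-cercariae rate over to female cercariae, which is an assumption. Across the confidence interval, the chance of 3/3 runs from 0.713³ = 0.36 to 0.9985³ = 0.996, and the chance of 10/10 from 0.713¹⁰ = 0.03 to 0.9985¹⁰ = 0.985. The protocol's own expectation of effects in nearly all volunteers points to the upper part of that range.

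**2. Room to rise with dose.** Take 94.1% in a group of 3 against 100% in a group of 10. Fisher's exact test gives p = 0.23 for 2/3 v 10/10 and p = 0.038 for 1/3 v 10/10, so it rejects only if at most 1 of the 3 is counted. That probability is 3 × (16/17) × (1/17)² + (1/17)³ = 49/4913 = 1.0%. For 10 v 10 it is about 0.01%. From a lower starting rate of 80% against 100%, the figures are 10.4% (3 v 10) and 3.3% (10 v 10).

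**3. Events that are not saturated.** For the syndrome, 2/3 = 66.7% and 2/11 = 18.2%. Fisher's exact p is (3 × 55 + 1 × 11)/1001 = 176/1001 = 0.18. If those were the true rates, Fisher power would be 17% (3 at the lower rate v 10 at the higher) and 40% (10 v 10). That is weak, but the proportion has ample room to move with dose. The two counts are not described in identical terms, so they illustrate room to move and do not estimate a dose effect.

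**4. What a duration summary could do.** The protocol gives no rash durations by dose, so no power can be derived for a comparison of days; any such figure would need an assumed ratio and spread. For two groups of 3, the smallest two-sided p of an exact rank test is 2/C(6,3) = 2/20 = 0.10. Fisher's test on 0/3 v 3/3 has the same floor of 0.10. Between successive groups of 3, neither measure can reach p < 0.05.

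**The case against.** The strongest reply is that the endpoint is frequency and severity, that the analysis summarises frequency and severity, and that duration was never part of the declared endpoint. On the natural reading, section 10.1.1 gives one proportion per grade, and only the mild one is near its ceiling. The more serious dose signal was in occurrence: section 13.1(b) says acute schistosomiasis syndrome was more frequent in the 30-cercariae group, which a proportion can show. The rashes were mild and needed no treatment. All of this stands, and it confines the point to the common mild reactions.

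A reader might infer that the primary safety result cannot separate doses at all, or that a longer burden at higher doses would go unnoticed in the trial. The documents support neither. The per-volunteer tabulation in section 10.1.1 has unspecified columns and could carry duration. The termination rule in section 8.7 uses persistence at grade 3 beyond 48 hours. Section 13.2 has the safety monitoring committee review all safety data before escalation. A listing is still not a by-dose summary, so the gap in the summary remains.

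It can also be said that worst-grade counting and by-symptom tables belong in a statistical analysis plan, which is not shown. Omitted table detail would indeed be no finding. Here, however, the protocol names the group-level measure and the tests, and the measure it names does not suit the reactions it expects most often.

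Finally, the analysis is mostly descriptive, so power is not the issue. That is right, and it is why the remedy should be descriptive too.

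**Conclusion.** The point holds in limited form. As worded, the by-dose summary in section 10.1.1 is close to uninformative for the common mild reactions and cannot show the effect on rash duration that section 13.1(i) reports. At 16/17, the chance that every volunteer is counted is 83% for a group of 3 and 55% for a group of 10. Even a rise to 100% at a higher dose would be detected with probability of 1% or less. This assumes that the rash rate with female cercariae is similar to that with male cercariae. The reported prolongation is itself tentative in the protocol and is given without figures.

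The moderate and severe proportions and the syndrome proportion are not affected. No sample size, error rate, escalation rule or termination rule depends on this. It is an inexpensive improvement to the summary of a main endpoint.

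**What to change.** In section 10.1.1:

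- State that each volunteer is counted once per solicited symptom (the list in section 8.3), at the worst grade among events judged possibly, probably or definitely related (section 9.2.5), with proportions shown by grade and dose. This settles the pooled-or-by-grade ambiguity and keeps near-universal rash apart from rarer, more severe events.
- Add a by-dose summary, as median and range, of days with each solicited symptom and days at grade 2 or above. Use the durations and changes in intensity recorded under section 9.2.4, and the diary. The diary is needed where section 9.2.4 has a diagnosis recorded in place of its component symptoms.
- State that the duration summary is descriptive and attach no power claim to it.

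The cost is a few sentences and one more table, from data already collected. Visits, sample size and clinical rules stay as they are.
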